## 5.2.6 Dose-Limiting Toxicity Evaluability

The evaluability rules for DLT assessment apply to dose-escalation cohorts only.

The DLT evaluation period is defined as the 4-week period after first study drug administration.

Patients evaluable for DLT must either a) receive at least 2 administrations of MP0317 at q3w dosing schedule or 3 administrations at q1w dosing schedule at the assigned dose level and be observed until pre-dose of Cycle 2 Day 8 or b) experience a DLT as defined in Section 5.2.5 during the DLT evaluation period.

A patient will not be considered as DLT evaluable and may be replaced if they experience any of the following events during the DLT evaluation period:

- Received an MP0317 dose which is less than 90% or more than 110% of the planned infusion dose.
- Discontinued from treatment due to AE or death unrelated to study treatment, withdrawal of consent, lost to follow-up or Investigator decision (unrelated to study treatment).

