### 5.2 Study Treatment Schedule and Administration

#### 5.2.1 Study Drug Dose

For each patient, the assigned dose of MP0317 will be based on the available cohort as recommended by the DERC. For the dose-escalation study part on a q3w schedule, the starting dose is 0.03 mg/kg q3w and up to 6 q3w dose levels are planned, as shown in Table 3. The doses to be evaluated on a q1w schedule in the dose-escalation part are shown in Table 3. A treatment cycle will be 3 weeks (21 days), with DLT evaluation period of 4 weeks after first study drug administration. See Section 5.2.9 for study treatment modifications.

[figure not shown]The table content is completely redacted with black boxes.

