**Table 3. Provisional Dose Levels for Dose-Escalation given Q3W or Q1W**

| Cohort Number   | Dose Level (mg/kg) | Dose schedule    | Number of Patients | Dose Level Increment (cumulative dose in mg/kg) |
|-----------------|--------------------|------------------|--------------------|-------------------------------------------------|
| -1 a | 0.01               | q3w              | 1 to 3             | - 66%                                           |
| 1               | 0.03               | q3w              | 1 to 3             | Starting dose                                   |
| 2               | 0.10               | q3w              | 1 to 3             | 233%                                            |
| 3               | 0.30               | q3w              | 3 to 6             | 200%                                            |
| 4               | 1.00               | q3w              | 3 to 6             | 233%                                            |
| 4b              | 0.50               | q1w b | 3 to 6             | 50% compared to 4                               |
| 5               | 3.00               | q3w              | 3 to 6             | 200% compared to 4                              |
| 5b              | 1.50               | q1w b | 3 to 6             | 200% compared to 4b                             |
| 6               | 10.00              | q3w              | 3 to 6             | 233% compared to 5                              |
| 6b              | 5.00               | q1w b | 3 to 6             | 233% compared to 5b                             |

a Dose level -1 represents a dose that may be evaluated if dose level 1 is poorly tolerated. No dose de-escalation below this level is planned. If dose level -1 is poorly tolerated, the study will be terminated.

b Initiated after DERC recommendation on the advice of the sponsor.

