**Table 16. Schedule of Assessments: Cycle 2 Detailed (Q1W)**

|         | Assessment Time Point                                                        | Physical Examination | Vital Signs and Pulse Oximetry | ECG a | Local Laboratory Safety Assessments | Pregnancy Test b | Urinalysis b , Thyroid Function | PK (Serum)   | Immunogenicity (ADA, Serum) | Blood Biomarkers (Serum, Plasma and/or Fresh Blood) | Tumor Assessment | Tumor Biopsy              |
|---------|------------------------------------------------------------------------------|----------------------|--------------------------------|------------------|-------------------------------------|-----------------------------|--------------------------------------------|--------------|-----------------------------|-----------------------------------------------------|------------------|---------------------------|
| Cycle 2 | Day 1, before start of infusion                                              | X                    | X (max -2 h)                   | X (max -2 h)     | X (max -48h)                        | X                           | X (max -48h)                               | X (max -2 h) | X (max -2 h)                | X (max -2 h)                                        |                  |                           |
|         | Day 1, start of infusion                                                     |                      | X (± 15 min)                   |                  |                                     |                             |                                            |              |                             |                                                     |                  |                           |
|         | Day 1, during infusion every 30 min                                          |                      | X (± 15 min)                   |                  |                                     |                             |                                            |              |                             |                                                     |                  |                           |

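### Section 5.2.6: on q1w, a partial fourth infusion makes a DLT-free patient non-evaluable while a missed one does not, and the synopsis definition of the DDS differs

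*Protocol*

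**What the plan says.** Section 5.2.6 has two parts.

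- **Qualifying criteria.** A patient without a DLT must "receive at least 2 administrations of MP0317 at q3w dosing schedule or 3 administrations at q1w dosing schedule at the assigned dose level". Follow-up has a fixed end as well: such a patient has to "be observed until pre-dose of Cycle 2 Day 8". A patient with a DLT in the window qualifies on that ground alone.
- **Exclusions.** The lead-in to the list runs "A patient will not be considered as DLT evaluable and may be replaced if they experience any of the following events during the DLT evaluation", meaning the 28-day window. The first event listed is that the patient "Received an MP0317 dose which is less than 90% or more than 110% of the planned infusion dose".

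The window is 28 days: "The DLT evaluation period is defined as the 4-week period after first study drug administration". Section 5.2.1 fixes the cycle: "A treatment cycle will be 3 weeks (21 days), with DLT evaluation period of 4 weeks after first study drug administration". Table 14 puts q1w infusions on Days 1, 8 and 15 of Cycle 1. Table 16 adds Cycle 2 Day 1 (its first row is "Day 1, before start of infusion"), which is study Day 22.

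Section 9.3.2 builds the dose-determining set (DDS) from Sections 5.2.5 and 5.2.6 and feeds it to the BLRM. The Protocol Summary defines the DDS by the two qualifying criteria only and does not mention the 90-110% limits.

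**The concern.** On q3w both planned infusions are required, so the minimum and the dose limits agree. On q1w the minimum leaves one infusion to spare, but the dose limits apply to every infusion received. A patient who has already met the minimum can therefore be disqualified by a further, partial infusion, and would have stayed evaluable had that infusion not been given.

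The rule decides who counts in the DDS. Table 3 plans 3 to 6 patients in each q1w cohort, so one patient is between 1/6 (17%) and 1/3 (33%) of the cohort's DLT information. Section 9.2.2 adds patients when fewer than 3 are evaluable at a dose level from cohort 3 upward, so losing one of 3 can require another enrolment. And because the Protocol Summary and Section 9.3.2 differ, the same patient is in the DDS under one and out under the other.

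**Working it through.** The protocol states no figure for this point, so there is none to reproduce. The check counts infusions and applies the rules.

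**1. Infusions planned before Cycle 2 Day 8 pre-dose (study Day 29).**
- q1w: Days 1, 8, 15, 22 = 4; required 3.
- q3w: Days 1, 22 = 2; required 2.

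**2. DLT-free q1w patients who stay on treatment.** Share of planned dose = sum of infusion fractions / 4.

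| Infusions (% of planned) | Share of window dose | 3 or more given | Any given dose below 90% | Section 5.2.6 | Protocol Summary |
|---|---|---|---|---|---|
| 100, 100, 100, 85 | 3.85/4 = 96.25% | yes | yes | out | in |
| 100, 100, 100, missed | 3/4 = 75% | yes | no | in | in |
| 90, 90, 90, missed | 2.7/4 = 67.5% | yes | no | in | in |

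In cohort 5b (1.50 mg/kg, so 4 x 1.50 = 6.0 mg/kg planned in the window), 3.85 x 1.50 = 5.775 mg/kg is dropped and 3 x 1.50 = 4.5 mg/kg is kept.

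**3. Do other readings remove the conflict?**
- *Missed infusion counted as a 0% dose:* every patient with three of four infusions then fails, so the minimum of three has no effect.
- *Limits applied to the total window dose:* three infusions at the 110% ceiling give 3.3/4 = 82.5%, still below 90%, so the minimum again has no effect.
- *Limits applied per infusion, as worded:* the inversion stands.

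**4. Direction of effect on the observed DLT rate.** Assume a true rate of 20%, short infusions unrelated to DLT, DLT patients retained, and a fraction x of DLT-free patients excluded. Observed rate = 0.20 / (0.20 + 0.80(1 - x)).
- x = 18.5%: 0.20/(0.20 + 0.80 x 0.815) = 23.5%.
- x = 34.4%: 0.20/(0.20 + 0.80 x 0.656) = 27.6%.

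On these assumptions the rate goes up.

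**5. Illustration of frequency.** The document gives no rate of short infusions. Assume p = 5% to 10% per infusion, independent between infusions.
- q1w, at least 1 of 4 short: 1 - 0.95^4 = 18.5%; 1 - 0.90^4 = 34.4%.
- q3w, at least 1 of 2 short: 1 - 0.95^2 = 9.8%; 1 - 0.90^2 = 19.0%.
- q1w, at least 2 of 4 short: 1.4% to 5.2%.

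If short infusions cluster completely within patients, the loss is 5% to 10% on either schedule.

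**The case against.** The two rules do different jobs. The 90-110% limits check that what was infused matches the assigned dose; the count of three is a minimum exposure. The BLRM covariate is the dose level, not the share of a 28-day total. The cumulative dose in Table 3 is per 21-day cycle (for 4b, 3 x 0.50 = 1.5 against 1.0, the stated 50% increase). On that basis three infusions in cohort 5b are 4.5 mg/kg, a full cycle. So accepting three of four is a deliberate tolerance, and the four-infusion denominator is this review's yardstick, not the protocol's. That stands. It does not explain why a patient who has met the minimum should lose evaluability by receiving part of one more infusion.

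The missed-infusion case is also narrow. Inability to give the next dose because of a drug-related AE can itself be a DLT under Section 5.2.5, and discontinuation for the unrelated reasons listed in 5.2.6 already makes a patient non-evaluable. What remains is a patient who stays on treatment and misses one infusion for a reason unrelated to the drug. Replacement is optional in 5.2.6, and excluded patients stay in the safety set and before the DERC. These limits are accepted.

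A reader might go further and infer that infusion reactions are the main source of short doses, so that the rule selects tolerant patients and understates the q1w DLT rate. The documents do not support this. Section 6.3 records a premedication recommendation and says nothing about incomplete doses. The Table 14 footnote requires complete administration, and Appendix 12.6 describes re-starting interrupted infusions. Removing only DLT-free patients shrinks the denominator. Retained patients with less exposure could pull the other way, but the net direction cannot be settled from the text. Nor do the documents show that the limits were written for q3w and carried over.

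**Conclusion.** The conflict is real and lies in the wording of Section 5.2.6. On q1w, a DLT-free patient at 96.25% of the planned window dose is excluded while one at 75% is included, and the Protocol Summary keeps both. This rests on the per-infusion reading, which the text supports, and on a short infusion at about 85%.

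The consequence is modest but concrete: informative DLT-free patients are lost without need from cohorts of 3 to 6, some may have to be replaced, and the DDS has two definitions. No understatement of the DLT rate should be claimed. The 19-34% loss is only an illustration under an assumed, independent 5-10% per-infusion rate and should not be quoted as an estimate. q3w is not affected by the inversion.

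**What to change.** Reconcile the two rules in Section 5.2.6 by tying the below-90% test to the required minimum. A DLT-free patient would be evaluable when at least 2 infusions on q3w, or 3 on q1w, were each at least 90% of the planned infusion dose, and an additional infusion below 90% would not by itself remove evaluability. Leave the above-110% rule as it is. Give the DDS definition in the Protocol Summary the same rule, and check that Section 9.3.2 points to it.

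The cost is one sentence in 5.2.6 and matching text in the Protocol Summary. No dose, schedule or procedure changes, and q3w is classified as before.

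There are two limits. Some DLT-free patients with a partial fourth infusion enter the DDS, but their exposure is no lower than that of the three-infusion patients already accepted. And the rule still counts adequate infusions rather than total dose: 100/100/85/85% (3.7/4 = 92.5%) stays out while 75% stays in. That follows from the plan's own choice of a minimum count and is at least applied consistently.

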|                          | 
schedule at the assigned dose level and are observed until pre-dose of Cycle 2 Day 8 or b) experience a DLT as defined in the protocol during the DLT evaluation period. The DLT evaluation period is defined as the 4-week period after first study drug administration. Patients who do not meet these minimum treatment and safety evaluation requirements will be regarded as ineligible for inclusion in the DDS and will be replaced if needed until the minimum number of patients required for evaluation is reached. The DDS will be used in the BLRM to estimate the dose-DLT relationship in the dose-escalation part of the study.
 
PK Set: All patients who received at least one dose of MP0317 and had at least one post-dose PK measurement.
 
Statistical methodology
 
The detailed methodology for summary and statistical analyses of the data collected in this study will be documented in a Statistical Analysis Plan (SAP).
Data will be analyzed and presented by dose level and study part.
 
Primary analysis
 
An adaptive BLRM guided by the Escalation With Overdose Control (EWOC) principle will be used in the dose-escalation part to determine the RDE (or MTD).
 
Safety analyses
 
Safety will be assessed through summaries of DLTs, AEs, SAEs, AESIs, AEs leading to treatment adaptation or study drug discontinuation, changes in laboratory parameters, changes in vital signs and ECGs and exposure to MP0317. For the dose-escalation part, the summary of DLTs will be performed using the DDS. Unless specified otherwise, all other safety analyses will be conducted for the SAS.
 
PK analyses
 
No formal statistical analysis beyond descriptive statistics is planned. For each PK parameter, individual and mean data and summary statistics will be presented.
 
Efficacy analyses
 
All efficacy analyses will be done according to investigator-assessed response criteria. The following antitumor activity endpoints will be analyzed and summarized for the SAS: ORR, BOR, DCR, DOR, TTP, PFS and OS.
 
Immunogenicity analyses
 
Incidence of ADA response and the potential correlation with PK, pharmacodynamic and safety parameters may be assessed.
 
Pharmacodynamic analyses
 
Summary statistics of pharmacodynamic markers will be reported.
 
Interim analyses
 
Each dose-escalation step is considered to be an interim analysis. The BLRM will be updated with the respective number of patients treated and the number of DLTs observed in the last cohort. The updated model will then give a statistical recommendation for the next escalation step. In addition, a risk-benefit assessment that includes a comprehensive analysis of safety and available clinical information will be done to decide on the next escalation steps.
 |

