|                                       | Grade 4 or recurrent Grade 3 (that cannot be adequately treated with standard-of-care)                                                                                                           | Permanently discontinue                                                                                                                                                                                                                                                                                                                                                                                                                             |
| CRS (Appendix 12.7)                   | Grade 1 to 3                                                                                                                                                                                     | Withhold until clinical improvement of symptoms according to Investigator judgement. Re-start at 50% of infusion rate of the current infusion and increase gradually.                                                                                                                                                                                                                                                                               |
|                                       | Grade 4 or recurrent Grade 3 (that cannot be adequately treated with standard-of-care)                                                                                                           | Permanently discontinue                                                                                                                                                                                                                                                                                                                                                                                                                             |

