### 9.3.2 Dose-Determining Set

The dose-determining set (DDS) will consist of all patients in the SAS, who meet the dose-limiting toxicity evaluability criteria in Sections 5.2.5 and 5.2.6. Patients who do not meet these minimum treatment and safety evaluation requirements will be regarded as ineligible for inclusion in the DDS and will be replaced if needed until the minimum number of patients required for evaluation is reached. The DDS will be used in the BLRM to estimate the dose-DLT relationship in the dose-escalation part of the study.

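### Section 5.2.6 contradicts itself on whether a patient with a DLT whose dose fell outside 90–110% of plan is DLT evaluable, and so on whether that DLT enters the BLRM

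*Protocol*

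**What the plan says.** Section 5.2.6 gives two routes to evaluability. Route a) requires a minimum number of administrations at the assigned dose level and observation to a set time point. Route b) requires only that the patient "experience a DLT as defined in Section 5.2.5 during the DLT evaluation period"; it sets no minimum dose.

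The exclusion list follows: "A patient will not be considered as DLT evaluable and may be replaced if they experience any of the following events" during the same period. Its first item is "Received an MP0317 dose which is less than 90% or more than 110% of the planned infusion dose". Its second begins "Discontinued from treatment due to AE or death unrelated to study treatment". The second item is tied to causes unrelated to treatment; the first is not tied to any cause.

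The DDS is defined in two places. Section 9.3.2 takes patients "who meet the dose-limiting toxicity evaluability criteria in Sections 5.2.5 and 5.2.6", so it carries both rules of 5.2.6. The Protocol Summary admits patients in the safety analysis set under route a) "or b) experience a DLT as defined in the protocol during the DLT evaluation period", with no 90%/110% rule. On use, Section 9.3.2 states: "The DDS will be used in the BLRM to estimate the dose-DLT relationship in the dose-escalation part of the study". The Protocol Summary also bases the dose-escalation DLT summary on the DDS.

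**The concern.** A treatment-related Grade 4 infusion reaction or cytokine release syndrome is a DLT under Section 5.2.5, and Table 4 has treatment permanently discontinued for it. If it arises during the infusion, the patient may have received less than 90% of the planned dose. Route b) then says evaluable and the exclusion list says not evaluable.

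If the exclusion prevails, removal depends on the outcome: the patient leaves the model because the toxicity stopped the infusion. The cohort may be completed with a replacement, and the BLRM sees fewer DLTs than occurred. That lowers the estimated overdose probability at the current and next dose. It also takes the event out of the DDS-based DLT summary, although DLT incidence is a primary endpoint.

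**Working it through.** **1. The texts side by side, for a patient with a DLT who received under 90% of plan**

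| Where stated | Result |
|---|---|
| 5.2.6, route b) | Evaluable |
| 5.2.6, exclusion list | Not evaluable, may be replaced |
| 9.3.2 | Refers to 5.2.5 and 5.2.6, so both answers |
| DDS definition in the Protocol Summary | Included |

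The same conflict arises above 110%, but there the dose deviation is not caused by the DLT.

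**2. Model inputs.** Section 9.4.1.2: logit p(d) = log α + β·log(d / 1 mg/kg). Table 23: log α ~ N(−2.685, SD 2), log β ~ N(−0.594, SD 0.5), correlation 0. Each cohort with r DLTs in n patients contributes p(d)^r·(1 − p(d))^(n − r). P(overdose at d) is the posterior probability that p(d) ≥ 0.33; Section 9.4.1.1 bars a dose when this exceeds 0.25.

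**3. Reproducing the plan.** Numerical integration over a grid gives prior overdose probabilities of 0.162, 0.263 and 0.396 at 1, 3 and 10 mg/kg, against 0.166, 0.267 and 0.401 in Table 24. For 1/3 at 1.00 mg/kg after 0/3 at each lower dose, it gives 0.303 at 3.00 mg/kg against 0.306 in Table 30.

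**4. A single DLT counted or lost.** There are 0/3 DLTs at every lower dose. Entries are P(overdose) at the next planned dose: Table 30 first, recomputed value in brackets. The 0/3 column is the DLT patient replaced by one without a DLT. The 0/2 column, recomputed only, is the patient dropped and not replaced.

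| Current → next (mg/kg) | 1/3, DLT counted | 0/3, replaced | 0/2, dropped | At the 0.25 limit |
|---|---|---|---|---|
| 0.03 → 0.10 | 0.261 (0.253) | 0.014 (0.015) | 0.022 | Narrowly barred becomes allowed |
| 0.10 → 0.30 | 0.193 (0.190) | 0.016 (0.016) | 0.021 | Allowed either way |
| 0.30 → 1.00 | 0.241 (0.237) | 0.032 (0.031) | 0.039 | Allowed either way |
| 1.00 → 3.00 | 0.306 (0.303) | 0.055 (0.053) | 0.066 | Barred becomes allowed |
| 3.00 → 10.00 | 0.384 (0.389) | 0.084 (0.085) | 0.105 | Barred becomes allowed |

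(For 0/3 at 0.30 mg/kg, Table 30 prints 0.063 in one column and 0.032 in another for the same next dose; both are below 0.25.) At 10.00 mg/kg there is no higher planned dose.

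**5. Two DLTs, one lost and replaced.** At 3.00 mg/kg, P(overdose at 3.00) falls from 0.411 (2/3) to 0.118 (1/3) in Table 30, recomputed as 0.414 and 0.120. The current dose moves from barred to permitted.

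**The case against.** The strongest reply is that the protocol does not say the patient is removed. Route b) has no dose condition, the Protocol Summary admits every patient with a DLT, and Section 5.2.7.1 bases the BLRM on any DLTs observed in the window. A reader might infer from the exclusion list that such DLTs are deleted as a settled rule. The documents do not support that: it is one of two readings. This part of the reply stands.

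The trigger is also narrow. Appendix 12.6 lets an interrupted infusion restart stepwise, Table 4 does the same for Grade 1 to 3 cytokine release syndrome, and a first Grade 3 infusion reaction that resolves under treatment is not a DLT. A DLT after complete infusions is unaffected. The protocol gives no frequency for the affected case, and it expects the drug's design to limit cytokine release syndrome, so this should not be described as losing an expected toxicity. Nor does losing one DLT always reverse a decision, as the 0.10 and 0.30 mg/kg rows show.

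Finally, there are safeguards. DLTs are reported within 24 hours, the dose-escalation review committee considers all safety information, and the Section 8.5 trigger of two or more patients with the same DLT is not tied to the DDS. These reduce the risk, but none returns the event to the BLRM. One provision works the other way: Section 5.2.7.1 lets escalation be considered with only two evaluable patients if neither has a related event of Grade 2 or higher, and an excluded DLT patient may not be counted among those two.

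**Conclusion.** The contradiction is real and bears on the analysis set that drives dose escalation. Section 5.2.6 gives opposite answers for the same patient, 9.3.2 carries both, and the Protocol Summary carries only the inclusive one. If the exclusion is followed, the bias is toward escalation. On the protocol's own figures the overdose probability at 3.00 mg/kg is 0.306 or 0.055 depending on the reading, a difference of 0.306 − 0.055 = 0.251 that straddles the 0.25 limit; at 10.00 mg/kg it is 0.384 or 0.084.

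These figures assume that the exclusion is the rule applied, that no DLTs occurred at lower doses, that cohorts have three patients, that any replacement has no DLT, and that the q3w prior of Table 23 holds. They do not carry over to q1w, whose prior is to be derived separately. The documents do not show that DLTs will be lost, or how often a DLT would leave a dose below 90%. They show only that the protocol does not prevent the loss.

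**What to change.** State in Section 5.2.6 that the 90%/110% exclusion applies only to patients who have not had a DLT in the evaluation period, so that route b) takes precedence. Align Section 9.3.2 with the DDS definition in the Protocol Summary, which already includes every patient with a DLT and has no dose rule to qualify.

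Entering the dose actually given into the BLRM for such patients is an optional modelling choice and is not needed to resolve the conflict.

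The cost is about one sentence in 5.2.6 and a matching edit in 9.3.2, with no extra patients, visits or assessments. It belongs in the protocol because evaluability and replacement are decided cohort by cohort during the trial.
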